### Laboratory analyses

Glucose as part of OGTT and IVGTT tests and HbA1c will be measured using either point-of-care analysers or local labs, depending on the site, in order to provide rapid feedback to participants to enable medical care. Urine ketones will be measured by dipstick in those with suspected diabetes in order to assess the need for short or long-term insulin replacement therapy. Serum lipase, CRP and lipids will be measured at accredited commercial laboratories. Fecal elastase will be measured at each site using stool preparation and ELISA kits from ScheBo (Biotech UK, Lyme Regis, UK).

Other laboratory assays (glucagon, insulin, pro-insulin, C-peptide, GIP, GLP-1 and auto-antibodies) for samples from Mwanza, Lusaka and the Philippines will be conducted together at Rigshospitalet, University of Copenhagen. Since it is not possible to ship samples from India to the UK, [name] of Rigshospitalet will arrange quality assurance with the Delhi laboratory.

### Data management

Data will be collected using computer-assisted personal interviews. Structured questionnaires programmed in
REDCap will be accessed by trained interviewers through tablets. Data will be transmitted to a secure database storage server hosted at the London School of Hygiene and Tropical Medicine (LSHTM). Quality control will be applied at each stage of data handling in accordance with Good Clinical Practice (GCP) requirements to ensure that all data are reliable and have been processed correctly. Access to the data (as uploaded in the database) will be granted to authorised representatives from the sponsor, host institution and the regulatory authorities to permit study-related monitoring, audits and inspections.

### Pre-processing of data and descriptive analyses

Fat and fat-free mass in kg will be divided by height in meters-squared, analogous to determining BMI from weight and height, to give fat mass index (FMI) and fat-free mass index (FFMI).

Socioeconomic status (SES) indices will be derived separately for each site using principal component analysis (PCA) of individual or family assets; the specific assets will differ by site since they have been chosen to be locally appropriate. The first component from the PCA will be divided into terciles for use in analyses.

Site-specific diet patterns will be calculated by PCA of food groups; the number of components to include will be based on eigenvalues and scree plots.
^
29
^ The level of adherence to individual patterns will be calculated by dividing the components in terciles.

Descriptive analysis will be conducted within cohorts and divided by sex. Means and standard deviations (SDs) will be used to summarise normally distributed data and medians and interquartile ranges (IQR) for non-normally distributed variables. Categorical variables will be described as proportions.

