## Abstract

**Background**:
Prenatal growth retardation may increase the risk of later chronic non-communicable diseases (NCDs), including diabetes; however, long-term effects of wasting malnutrition in childhood or adulthood are less studied. Pancreatic exocrine and endocrine functions, both critical for nutrition and NCD aetiology, may not fully recover following malnutrition. However, the evidence and mechanistic information is piecemeal. We hypothesise that wasting malnutrition at any age has long-term detrimental effects on endocrine and exocrine pancreatic structure and function.

**Methods: **The SAMPA international research programme will assess pancreatic structure and function in 3700 participants from ongoing observational nutrition cohorts, two adolescent and four adult, in Zambia, Tanzania, Philippines, and India. Pancreas size, structure, and calcification will be assessed by ultrasound and computed tomography (CT) scan; exocrine function by faecal elastase and serum lipase; and endocrine function by haemoglobin A1c (HbA1c) and blood glucose, insulin and C-peptide concentrations during an oral glucose tolerance test (OGTT). In-depth hormonal analyses of incretins, glucagon, proinsulin and trypsinogen during OGTT and intravenous glucose tolerance tests will be done in subsets of adult participants. Pancreatic size and function outcomes will be compared between people with and without prior wasting malnutrition. Analyses will investigate effect modification by sex, current age, time since malnutrition, current body mass index and dietary patterns. Mathematical modelling of OGTT data will be used to estimate the relative contribution to glucose dysregulation of decreased insulin production, changes in insulin clearance and increased insulin resistance. Proinsulin/insulin ratio will be analysed in archived samples from the Tanzanian cohort using a nested case-control design to investigate whether abnormal values precede diabetes.

**Conclusions:** SAMPA, a large-scale multi-centre research programme using data from people with or without prior wasting malnutrition to assess several aspects of pancreatic phenotype, will provide coherent evidence for future policies and programmes for malnutrition and diabetes.

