### Statistical analyses and sample size calculations

Analyses related to individual hypotheses are described below. Primary analyses will be conducted for each cohort separately. Pooled analyses using all or some cohorts combined will be conducted based on the individual cohort results, and in order to investigate how age at malnutrition and length of time between malnutrition and outcome assessment influence the associations between malnutrition and pancreas structure and function. Analyses will be guided by the conceptual framework in
Figure 1. Sample sizes for the specific hypotheses indicate that, with the available number of participants in the cohorts, we have sufficient power for the main analyses with all participants. For some expensive or labour- and participant-intensive outcomes, we had to consider cost and feasibility and have calculated power for analyses in subsets.

*Hypothesis 1:*
Prior malnutrition is associated with later abnormal pancreatic structure and endocrine and exocrine function.

Participants with and without prior wasting malnutrition, the SAMPA study primary exposure, will be compared within each cohort for all pancreas structure and function outcomes: diabetes by OGTT or HbA1c, exocrine function as indicated by faecal elastase and serum lipase, and pancreas size and presence of abnormalities detected by ultrasound or CT scan. We will initially fit regression models for each outcome with prior malnutrition as the main exposure, controlling for sex and for age as a continuous variable. We will investigate whether there are interactions between prior malnutrition and sex, which is known to be associated with both prior malnutrition and diabetes. We will then investigate whether the associations between malnutrition and the outcomes differ by the following variables:
•Time since malnutrition•Sitting/standing height ratio as an indicator of early life stunting•HIV status for African cohorts only (SAM Lusaka, NUSTART Lusaka, CICADA)

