Several variables – BMI, FMI, FFMI and diet pattern (using components from PCA as defined above) – have potentially complex relationships with the exposure and outcomes. These variables will be measured at the time of outcome assessment, but are assumed to reflect participants’ nutritional status and diet prior to the outcome. We will start by investigating the associations among diet patterns, BMI, FMI and FFMI at the time of pancreas testing. We will then explore several relationships between these variables, the prior malnutrition exposure, and the outcomes. First, BMI and FMI may be on the causal pathway from wasting malnutrition to diabetes since recovery from wasting malnutrition associated with infection may lead to excess fat deposition,
^
30
^
^,^
^
31
^ and since people previously severely malnourished may, if it becomes possible later, choose to gain weight as a buffer against future food shortages. Second, BMI, FMI and diet patterns could be modifiers of the association between prior malnutrition and diabetes, as seen previously for diet pattern and BMI in Chinese famine survivors.
^
32
^ Third, exocrine pancreas abnormalities which result in fat malabsorption or intestinal discomfort may induce participants to modify their diets which could result in changes to BMI, FMI or FFMI.

We will conduct exploratory analyses to investigate the mechanisms through which the exposure variable, malnutrition, is associated with pancreas outcome variables. For example, decreased production of incretins by gut epithelial cells may be associated with both exocrine pancreas function, which could affect rate of absorption of nutrients which trigger incretin secretion, and insulin secretion.

**
*Sample size*
**: Large variations in prevalence of impaired glucose tolerance (OGTT≥7.8 mmol/L
*)* or high fasting glucose in never malnourished (2%-11%) make estimates imprecise. The absolute difference in prevalence of hyperglycaemia in those with prior malnutrition versus those without was 3% to 9% in these studies.
^
32
^
^–^
^
34
^ Assuming an intermediate prevalence of OGTT ≥7.8 mmol/L of 7% in those without malnutrition, the CICADA and St-ATT cohorts individually have 80% power to detect a difference in prevalence of 7.5% in those with malnutrition. For continuous variables,

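### The plan cuts PCA scores into terciles without settling whether diet pattern is modelled as a continuous score or in thirds; thirds would lose about 21% of the information in a normal score

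*Protocol article*

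**What the plan says.** The section on pre-processing and descriptive analyses derives two kinds of score by site-specific principal component analysis.

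- **Socioeconomic status.** "The first component from the PCA will be divided into terciles for use in analyses".
- **Diet pattern.** Several components may be kept, and "The level of adherence to individual patterns will be calculated by dividing the components in terciles".

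Neither sentence gives a reason for the cut.

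The Hypothesis 1 text under statistical analyses brings diet in as "diet pattern (using components from PCA as defined above". It then lists several relationships to explore, one of which is that "BMI, FMI and diet patterns could be modifiers of the association between prior malnutrition and diabetes". The abstract announces the same aim: "Analyses will investigate effect modification by sex, current age, time since malnutrition, current body mass index and dietary patterns".

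The initial regression models are described as "controlling for sex and for age as a continuous variable". Socioeconomic status does not appear in them or in any other model in the article. No cut is stated for age, BMI, FMI or FFMI.

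**The concern.** A component score is continuous. Cutting it into thirds treats everyone within a third as identical. The interaction test then either spends two degrees of freedom or becomes a trend over three codes.

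Effect modification by diet is an announced aim. Primary analyses are run cohort by cohort, and the smallest cohorts are expected to have 180, 300 and 420 participants. A coding that discards information makes a real modification easier to miss.

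The article also leaves open which coding is meant. The back-reference in the Hypothesis 1 text could point to the component itself or to the terciled adherence level. Two analysts could follow the text faithfully and fit different models.

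For socioeconomic status the tercile rule is explicit. If the tercile were used as a covariate, confounding within terciles would remain.

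**Working it through.** **No figure of the plan to reproduce.** The article gives no power, effect size, significance level or degrees of freedom for any diet or socioeconomic analysis. Its statement for the binary outcome, "the CICADA and St-ATT cohorts individually have 80% power to detect a difference in prevalence of 7.5% in those with malnutrition", concerns the main effect of malnutrition. It cannot be carried over to an interaction.

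**Inputs.** The tercile rules come from the pre-processing section. Assumed here: a normal score, a linear modification, a two-sided 5% level, and a range of values for the power of the continuous test.

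**Step 1: information kept by terciles.** The upper cut of a standard normal score is z(2/3) = 0.431, where the density is 0.3636.

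- Mean of the upper third: 0.3636 / (1/3) = 1.091. The lower third has mean −1.091 and the middle third 0.
- Between-third variance: (2/3) × 1.091² = 0.793.

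So 79.3% is kept and 20.7% lost.

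**Step 2: other score shapes** (one million simulated values each, terciles as categories).

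| Shape | Information lost |
|---|---|
| Uniform | 11% |
| Normal | 21% |
| Gamma, skew 1 | 25% |
| t, 5 df | 31% |
| Lognormal, skew about 1.8 | 33% |
| Exponential | 35% |

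**Step 3: power.** Take the non-centrality that gives the assumed power with 1 df, multiply it by 0.793, and read off power with 1 df (trend) and 2 df (categories). At 80% the non-centrality is (0.842 + 1.960)² = 7.85, and 7.85 × 0.793 = 6.23.

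| Assumed power, continuous 1-df test | Tercile trend, 1 df | Loss (points) | Tercile categories, 2 df | Loss (points) |
|---|---|---|---|---|
| 20% | 16.8% | 3 | 13.1% | 7 |
| 30% | 24.8% | 5 | 19.1% | 11 |
| 50% | 41.5% | 9 | 32.6% | 17 |
| 80% | 70.4% | 10 | 60.1% | 20 |
| 90% | 82.3% | 8 | 73.6% | 16 |
| 99% | 96.8% | 2 | 93.8% | 5 |

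**Step 4: simulation check.** The malnutrition-by-score interaction was simulated in a linear model, 2000 runs per setting, at the effect size giving about 80% power. Exposed shares come from the article's cohort table: (189 + 216)/900 = 45% for St-ATT and 635/1951 = 32.5% for CICADA (BMI below 18.5 kg/m² in both).

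| Setting | Continuous | Trend | 2 df |
|---|---|---|---|
| n = 600, 45% exposed | 0.80 | 0.69 | 0.60 |
| n = 1412, 32.5% exposed | 0.79 | 0.70 | 0.60 |

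These agree with Step 3.

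**Step 5: where the 2-df loss comes from.** Keep the full non-centrality of 7.85 but spend 2 df, as a joint linear-plus-quadratic test of the continuous score would. Power is 70.9%. Of the 19.9 points lost at 80%, 80.0 − 70.9 = 9.1 are due to the extra degree of freedom and 70.9 − 60.1 = 10.8 to the lost information.

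**The case against.** **The diet models may not use terciles at all.** The tercile sentence sits in a pre-processing and descriptive section and defines a level of adherence. The analysis text speaks of components, and functional form is often left to a statistical analysis plan, which is not shown here. This stands in part: it is not established that diet is cut before modelling. What remains is that the article states a tercile definition, refers back to it, and does not say which form is modelled.

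**A reader might infer that the trial loses 10 to 20 points of power.** The documents do not support that. It needs a continuous test with power in the middle-to-upper range, and the article gives no interaction power. If interaction power is low, as it may well be in the small cohorts, the loss is nearer 3 to 7 points. Nearly half of the 2-df figure at 80% is the price of a degree of freedom, which a joint linear-and-quadratic interaction would pay too.

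**A reader might infer that socioeconomic confounding is left uncontrolled.** No model names socioeconomic status, so this can only be said conditionally.

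**Terciles have some merits.** They can pick up a non-linear pattern, and site-specific ranks are a defensible way to handle asset lists that differ by site. Both are fair, but standardised site-specific scores also serve the second purpose, and a separate check for non-linearity serves the first without discarding information in the main test.

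**The consequence is small.** Diet modification is one of several exploratory relationships, and pooled analyses are also foreseen. This stands and limits the importance of the point.

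**Conclusion.** The point holds as a minor one, in two parts. First, the pre-processing section and the Hypothesis 1 text do not together settle whether diet pattern is modelled as a continuous component or in terciles. Second, if terciles are modelled, about 21% of the information in the score is lost for a normal score with a linear effect, and about 11% to 35% over the other shapes tried. The article gives no score distribution, so the single figure should not be read as exact.

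The power cost for the diet interaction runs from a few points to about 20, depending on the unstated power of the continuous test and on whether a trend or a 2-df test is used. A threshold or other non-linear modification would change these figures.

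For socioeconomic status the concern is residual confounding within terciles, and only if the tercile is used as a covariate. The malnutrition comparison adjusted for sex and continuous age does not involve either score and is untouched.

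**What to change.** State in the analysis text that standardised continuous PCA scores enter the models, for diet patterns and for socioeconomic status wherever it is used. Name the 1-df linear malnutrition-by-diet interaction as the main test of diet modification. Check non-linearity separately with a quadratic or restricted cubic spline term, so that the check does not cost the main test a degree of freedom. Keep terciles for descriptive tables and for displaying estimates by level of adherence. Reword the pre-processing sentences and the back-reference in the Hypothesis 1 text so that they name the same form.

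The cost is a sentence or two and no new data. The one downside is that a linear main test can miss a threshold pattern, which the separate check is there to cover.

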### Statistical analyses and sample size calculations

Analyses related to individual hypotheses are described below. Primary analyses will be conducted for each cohort separately. Pooled analyses using all or some cohorts combined will be conducted based on the individual cohort results, and in order to investigate how age at malnutrition and length of time between malnutrition and outcome assessment influence the associations between malnutrition and pancreas structure and function. Analyses will be guided by the conceptual framework in
Figure 1. Sample sizes for the specific hypotheses indicate that, with the available number of participants in the cohorts, we have sufficient power for the main analyses with all participants. For some expensive or labour- and participant-intensive outcomes, we had to consider cost and feasibility and have calculated power for analyses in subsets.

*Hypothesis 1:*
Prior malnutrition is associated with later abnormal pancreatic structure and endocrine and exocrine function.

Participants with and without prior wasting malnutrition, the SAMPA study primary exposure, will be compared within each cohort for all pancreas structure and function outcomes: diabetes by OGTT or HbA1c, exocrine function as indicated by faecal elastase and serum lipase, and pancreas size and presence of abnormalities detected by ultrasound or CT scan. We will initially fit regression models for each outcome with prior malnutrition as the main exposure, controlling for sex and for age as a continuous variable. We will investigate whether there are interactions between prior malnutrition and sex, which is known to be associated with both prior malnutrition and diabetes. We will then investigate whether the associations between malnutrition and the outcomes differ by the following variables:
•Time since malnutrition•Sitting/standing height ratio as an indicator of early life stunting•HIV status for African cohorts only (SAM Lusaka, NUSTART Lusaka, CICADA)

Several variables – BMI, FMI, FFMI and diet pattern (using components from PCA as defined above) – have potentially complex relationships with the exposure and outcomes. These variables will be measured at the time of outcome assessment, but are assumed to reflect participants’ nutritional status and diet prior to the outcome. We will start by investigating the associations among diet patterns, BMI, FMI and FFMI at the time of pancreas testing. We will then explore several relationships between these variables, the prior malnutrition exposure, and the outcomes. First, BMI and FMI may be on the causal pathway from wasting malnutrition to diabetes since recovery from wasting malnutrition associated with infection may lead to excess fat deposition,
^
30
^
^,^
^
31
^ and since people previously severely malnourished may, if it becomes possible later, choose to gain weight as a buffer against future food shortages. Second, BMI, FMI and diet patterns could be modifiers of the association between prior malnutrition and diabetes, as seen previously for diet pattern and BMI in Chinese famine survivors.
^
32
^ Third, exocrine pancreas abnormalities which result in fat malabsorption or intestinal discomfort may induce participants to modify their diets which could result in changes to BMI, FMI or FFMI.

We will conduct exploratory analyses to investigate the mechanisms through which the exposure variable, malnutrition, is associated with pancreas outcome variables. For example, decreased production of incretins by gut epithelial cells may be associated with both exocrine pancreas function, which could affect rate of absorption of nutrients which trigger incretin secretion, and insulin secretion.

**
*Sample size*
**: Large variations in prevalence of impaired glucose tolerance (OGTT≥7.8 mmol/L
*)* or high fasting glucose in never malnourished (2%-11%) make estimates imprecise. The absolute difference in prevalence of hyperglycaemia in those with prior malnutrition versus those without was 3% to 9% in these studies.
^
32
^
^–^
^
34
^ Assuming an intermediate prevalence of OGTT ≥7.8 mmol/L of 7% in those without malnutrition, the CICADA and St-ATT cohorts individually have 80% power to detect a difference in prevalence of 7.5% in those with malnutrition. For continuous variables,
*i.e.* glucose, hormones, faecal elastase and serum lipase, the available sample size in the smallest cohort will be sufficient to determine differences of 0.4 times the standard deviation with 90% power. Expected differences in pancreas volume were calculated using volume normalised to kg body weight to account for the participant age and size range.
^
35
^ A total of n=100 per cohort (assuming a standard deviation of 0.3 mL/kg) will provide 90% power to detect differences of 0.2 mL/kg between those with/without prior malnutrition, which is a smaller difference than that expected between people with and without diabetes.
^
35
^
^,^
^
36
^

*Hypothesis 2:*
Prior malnutrition is associated with pancreatic calcification which in turn is associated with diabetes.

To investigate whether prior malnutrition is associated with pancreas calcification, from each adult cohort we will randomly select for CT scans 50 participants who were exposed to malnutrition and 50 controls who were not exposed. The presence of calcification or other pancreas abnormalities on CT will be compared between those with or without prior malnutrition.

In order to increase sample size for this and for the second part of the hypothesis comparing calcification with diabetes, results from CT scans in the subset of participants with these will be compared with the ultrasound results from the same participants to indicate whether abnormalities determined by ultrasound, e.g. pancreas body or duct shape, correspond to calcification by CT scan. We will then compare the proportion of abnormalities based on ultrasound or CT scan among those with and without diabetes.

**
*Sample size*
**: Population prevalence estimates for pancreatic calcification appear unavailable so we have not performed any sample size calculations. Pancreatic calcifications are seen in fibro-calculous pancreatic diabetes
^
7
^ but these studies have been conducted on participants selected for their clinical presentation.

*Hypothesis 3:*
The abnormal glucose regulation seen after malnutrition is associated with relative insulin deficiency with or without insulin resistance.

A deeper understanding of associations between prior malnutrition and the underlying glucose metabolic pathways will be explored through modelling biochemical measures over the course of the two-hour OGTT. Glucose, insulin and C-peptide data from OGTT will be used to model pancreatic cell functionality according to published methods in order to determine a set of indices quantifying: first phase, second phase, and total insulin secretion,
^
37
^ whole-body and hepatic insulin clearance,
^
38
^ and insulin sensitivity.
^
25
^
^,^
^
39
^ For the child cohorts for whom only three blood samples are available over the two-hour OGTT, we will use methods designed to determine insulin sensitivity from sparsely sampled OGTTs.
^
26
^ The IVGTT data from the CICADA cohort subset can be similarly modelled to estimate insulin sensitivity and insulin secretion. Comparison of the indices estimated from the two tests will provide information as to whether altered intestinal function,
*e.g.* glucose absorption or incretin secretion, influences insulin secretion or sensitivity in participants previously malnourished or not.

**
*Sample size*
**: We will use individual data from all SAMPA adult participants and, for children who have only three sample points during OGTT, we will combine data from groups of participants.
^
26
^ Most previous studies in this area include 10-100 people per group, whereas we will be able to study all SAMPA participants.

*Hypothesis 4:*
An abnormal fasting pro-insulin/insulin ratio is associated with later development of diabetes in adults who had malnutrition and infection.

**
*Analysis*
**: We will use the detailed data and samples available from CICADA to investigate whether the proinsulin/insulin ratio in CICADA samples collected from fasted participants about four years prior to the SAMPA visit is associated with diabetes or prediabetes at the SAMPA visit. This will be a nested case-control study where cases are 60 CICADA participants with current diabetes by OGTT and controls are 60 CICADA participants with normal OGTT. These participants will be selected by stratified random sampling. Logistic regression will be used, controlling for age and sex, to determine if prior proinsulin/insulin ratio is associated with later diabetes.

**
*Sample size*
**: The sample size was a function of available cases and consumable costings. A sample of 120 (1:1 ratio of cases and controls) will provide 90% power to detect a difference of 0.04 in the fasting proinsulin/insulin ratio (assuming an SD of 0.07) which is smaller than that found between people with and without type 2 diabetes.
^
40
^

